**Fig. 3 Fig3:**
[figure not shown]
Data flow. Clinical data are entered into the eCRF by the local investigators at the study site and by the parents into the SaVeBRAIN.Kids parent app. The eCRF for the physician interface contains mainly single- or multiple-choice options and includes plausibility ranges and cross validation for continuous data. Pseudonymized clinical data from the eCRF and parent app are stored on a server at Hof University and forwarded to the TTP. The study sites transmit patient data and corresponding pseudonyms to the patients’ respective health insurances, who in return transmit billing data to the TTP for merging with clinical data based on the pseudonyms. After resolving plausibility issues, the final datasets will be forwarded to the clinical and economic evaluators for their planned analyses. The parent survey for process evaluation will collect pseudonymized answers via an online survey hosted by EsFoMed. To enable descriptive and adjusted analyses, the TTP will forward basic demographic information to EsFoMed. Staff surveys will be collected via an anonymous online survey hosted by EsFoMed. For all survey data, plausibility checks will be performed by EsFoMed

Monthly audits will ensure that recruitment targets are met, and appropriate individualized measures will be undertaken to enhance recruitment if necessary. Regular plausibility checks of entered clinical data including audit trails will be applied to ensure data quality. For health insurance data, plausibility and quality checks will be conducted at the TTP and issues resolved in bilateral correspondence with the respective health insurance company. For survey data, plausibility checks will be performed by the Institute for Health Care Management and Research. Additional data cleaning will be performed as necessary before analyses by the respective evaluators if not done by the TTP a priori.

#### Statistical methods

##### Clinical evaluation

For the hospitalized patient group, the relative risk change due to the nCP for the binary endpoint “hospitalization” will be estimated using a GLMM with log link and modeling fixed effects for intervention and time as well as random study site effects. A Wald Z-test will be used to test the null hypothesis of equal hospitalization risk with and without the intervention at a significance level of *α* = 0.05. For the non-inferiority analysis with respect to the proportion of patients with unplanned re-visits, the absolute risk difference will be considered. A GLMM with an identity link for the binary endpoint of unplanned re-visits, again with fixed effects for intervention and time and random study site effects, will be applied. A one-sided 97.5% confidence interval will be estimated for the difference in unplanned re-hospitalization rates. If the non-inferiority margin is not overlapped by the confidence interval, the null hypothesis of inferiority will be rejected. The two endpoints will be tested co-primary, i.e., both statistical tests have to be significant for a study success. As co-primary testing does not inflate the type I error rate, there is no need to correct for multiple testing, while an overall power of more than 80% can be preserved assuming that the two tests are independent each with a power of 90% (power of 1 st COP times power of 2nd COP).

Secondary outcomes will be analyzed using appropriate statistical methods as specified in the statistical analysis plan (SAP) prior to the beginning of the study. Clinical documentation will be performed in the software tools designed for the SaVeBRAIN.Kids study to ensure high data quality.

Primary analyses will be conducted as intention to treat, comparing outcomes in patients recruited before and after the study sites’ staff introduction to the nCP according to the randomization. Study sites with major protocol violations (e.g., late or no training for the nCP) will be excluded from a sensitivity analysis of a per-protocol study population. Further details will be specified in the SAP.

Due to the very short observation period for the primary outcomes, a drop-out rate of less than 5% is assumed. The primary analyses will thus be conducted as complete-case analysis. Sensitivity analyses will be conducted in which missing primary outcomes will be replaced with either a success (best-case scenario) or failure (worst-case scenario). The reason for missing values in the primary outcomes will also be recorded. In the unexpected case that more than 5% of values are missing, it will be possible to differentiate whether the missing data is likely to be Missing at Random (MAR) or Missing Not at Random (MNAR). For observations with more than 5% values missing under the MAR assumption, multiple imputation methods may be applied, and the results compared with the complete-case analysis. Further handling of missing data will be defined in the SAP.

To detect changes that may result from increased awareness merely due to study participation, anonymous retrospective data collection is carried out in terms of a historical control cohort, covering a 12-month period before the beginning of the project at each study site. In this case, the outcome parameter is the relative number of hospitalizations out of the total number of cases that would potentially meet the study’s inclusion criteria. This measure does not prevent potential bias but helps to detect potential bias, thereby supporting the interpretation of results.

##### Healthcare economic evaluation

A cost-minimization analysis with the nCP versus standard care will be conducted using health insurance billing data covering the period 1 week before and after the trauma, with a sensitivity analysis covering 1 month before and after the trauma. Alternatively, a cost-effectiveness analysis (CEA) can be conducted if the assumed non-inferiority of the nCP is not demonstrated in the clinical study. The comparison will be made using a Difference-in-Differences approach, with the cost-minimization analysis comparing only costs, and the CEA calculating the incremental cost-effectiveness ratio (ICER). Sensitivity analyses will be conducted to account for uncertainties in both approaches.

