##### Secondary outcomes

Secondary hospitalization following initial outpatient management, re-visits (all-cause and TBI-related), missed clinically relevant intracranial injury, admission to intensive care unit, neurosurgical intervention, death, costs/cost-effectiveness, acceptance, and barriers to implementation.

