#### Sample size calculation

The sample size calculation considered both CPOs, using generalized linear mixed models (GLMM) for both analyses. To estimate the relative risk of hospitalization, a GLMM with log link is planned. The calculation is based on hospitalization data from 2022 (ICD-10 German modification S02.- and S06.-) from 14 study sites that provided ED data on ambulatory care and hospitalizations during the pre-planning of the study with a mean admission rate of 61% (range [22%, 93%]). For the sample size calculation, a mean hospitalization rate of 50% was assumed to account for possible changes in hospitalization behavior due to implementation training or fluctuating admission capacities. The study’s aim is a relative risk reduction of 20% (relative risk = 0.8). The GLMM also requires the intra-cluster correlation coefficient (ICC), which is estimated at 0.142 based on available data (Fleiss-Cuzick estimator) and set at 0.15 for the calculation. With a power of 0.9, *α* = 0.05, and 11 study sites a sample size of 1056 patients is required for the first CPO.

The second CPO is examined using a non-inferiority test. A GLMM with identity link will be applied to estimate the risk difference. Based on an unplanned re-visit rate of 6% in one of the participating study sites and literature-reported rates of 1.5% [11], an average unplanned re-visit rate of 3% is assumed before the intervention. A 2-percentage point increase in unplanned re-visits during the intervention is anticipated due to potentially increased parental need for reassurance. In addition, a 5-percentage point increase in unplanned re-visits is considered medically acceptable, as patients would otherwise still be in hospital, and spot-ED presentations are considered less burdensome than hospitalization. Thus, an unplanned re-visit rate in the nCP that ≤ 7 percentage points above standard care is considered non-inferior. With an assumed ICC of 0.1, power of 0.9, *α* = 0.025, and 11 participating study sites, a sample size of 1320 (10 per study site per month) is needed. Due to the very short observation period, a drop-out rate of 5% is assumed, resulting in a required sample size of 1390 (11 per study site per month).

The leading sample size is derived from the non-inferiority testing plus the assumed dropout rate is established as the recruitment target for the prospective clinical study.

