## Discussion

The SaVeBRAIN.Kids trial addresses a relevant healthcare challenge in Germany, where hospitalization rates for pediatric TBI drastically exceed rates in similar healthcare systems. The disparity likely reflects the use of non-standardized care pathways along with economic incentives posed by the diagnose related group reimbursement system. The study will be conducted using a cluster-randomized stepped-wedge design, allowing to integrate the novel care pathway into existing clinical settings at the same time as levelling out seasonal variations of TBI incidence.

Within the German healthcare system, the nCP represents a paradigm shift in mild TBI management for low-risk pediatric, emphasizing standardized assessment, structured observation in the emergency department, and technology-assisted home monitoring. This approach aligns with up-to-date international best practice while addressing country-specific decision-making processes that cause high hospitalization rates. By relying on evidence-based risk stratification and implementing standardized treatment/monitoring protocols, we aim to maintain medical safety while reducing unnecessary hospitalizations.

The dual co-primary outcome design balances effectiveness (hospitalization rate) with safety (unplanned re-visits), reflecting the need to achieve both cost-efficiency and non-inferiority with respect to clinical outcomes. The comprehensive economic evaluation will provide important information on cost-effectiveness that could inform broader implementation decisions for implementation into routine care. Including retrospective data analysis and process evaluation strengthens the study by providing context to interpret results and identify implementation barriers.

Limitations of the study include the lack of blinding during the intervention for both clinicians and parents, which is unavoidable given the study design. Additionally, the 72-h follow-up period may not capture all delayed complications, making an additional passive surveillance necessary. For the current study, the data entered into the parent app will not be viewable in real-time by the attending physicians to avoid the app falling under the medical device regulation of the EU. For future commercialization and implementation into routine care as a medical product, the integration of real-time data collection via the parent app may represent a particularly innovative approach to post-discharge surveillance.

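### When non-inferiority is shown, the planned economic evaluation compares costs only, so the listed cost-effectiveness outcome is not estimated in a successful trial, although the plan allows for unequal re-visit rates

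*Protocol article*

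**What the plan says.** The section Healthcare economic evaluation names a cost-minimization analysis of the novel pathway against standard care, based on insurance billing data, as the planned analysis. It continues: "Alternatively, a cost-effectiveness analysis (CEA) can be conducted if the assumed non-inferiority of the nCP is not demonstrated in the clinical study". Both would use a difference-in-differences approach, "with the cost-minimization analysis comparing only costs, and the CEA calculating the incremental cost-effectiveness ratio (ICER"). Sensitivity analyses are announced for both approaches but not described.

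The section Sample size calculation gives the expected effects. For the second co-primary outcome, "an average unplanned re-visit rate of 3% is assumed before the intervention", and "A 2-percentage point increase in unplanned re-visits during the intervention is anticipated due to potentially increased parental need for reassurance". The margin follows: "Thus, an unplanned re-visit rate in the nCP that ≤ 7 percentage points above standard care is considered non-inferior". For the first co-primary outcome the aim is a relative risk of hospitalization of 0.8 from an assumed 50%.

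The section Secondary outcomes lists "costs/cost-effectiveness, acceptance, and barriers to implementation". The Discussion states, without condition: "The comprehensive economic evaluation will provide important information on cost-effectiveness".

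**The concern.** A cost-minimization analysis answers the economic question only if the two pathways have the same outcomes. A non-inferiority result does not establish that. It shows that the increase in re-visits is unlikely to exceed the margin, and this trial is sized to show it when the increase is truly 2 points. The plan also hopes for a clear difference in the other direction on admissions. It defends its margin as a trade-off, with extra ED visits judged less of a burden than a hospital stay. Setting such effects against each other and against cost is the task of a cost-effectiveness analysis; a comparison of costs alone cannot do it.

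At stake is the economic conclusion, not the co-primary results. If the trial succeeds and adoption is considered, the economic evaluation as written would give a cost difference but no incremental cost per unit of effect and no joint uncertainty. The kind of economic result would also change according to which side of the margin one confidence limit falls.

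**Working it through.** **Inputs** (Sample size calculation, Interventions and Statistical methods): 11 sites, 12 months, one site switching per month; 10 patients per site per month; ICC 0.1; control rate 3%; anticipated increase 2 points; margin 7 points; one-sided alpha 0.025; power 0.9; dropout 5%. The standard stepped-wedge variance formula (Hussey and Hughes) is my assumption, since the article does not name its method.

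**1. Reproducing the plan's sample size.** Sites contribute 11, 10, ..., 1 intervention months, so U = 66 and the sums of squares over periods and over sites are W = V = 506. With I = 11, T = 12, s = within-site variance/m and between-site variance t:

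Var = I·s·(s + T·t) / [(I·U − W)·s + (U² + I·T·U − T·W − I·V)·t]

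- Total variance at the control rate: 0.03 × 0.97 = 0.0291, so t = 0.1 × 0.0291 = 0.00291 and s = 0.9 × 0.0291/10 = 0.002619.
- I·U − W = 726 − 506 = 220. The second bracket is 4356 + 8712 − 6072 − 5566 = 1430.
- Var = 11 × 0.002619 × 0.037539 / (0.57618 + 4.1613) = 0.000228, so SE = 1.51 points.
- Power = Φ((7 − 2)/1.51 − 1.96) = 0.911. With 9 per site per month it is 0.883, so 10 is the smallest whole number that reaches 0.90: 11 × 12 × 10 = 1320.
- Dropout: 1320/0.95 = 1389.5, rounded up to 1390.

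Both stated figures are reproduced, and they require the 2-point increase to be built in: the distance to the margin is 5 points, not 7.

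**2. How often the cost-only branch is taken at the planned +2 points.**

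| Variance taken at | SE (points) | P(non-inferior) | Largest observed increase still non-inferior, 7 − 1.96·SE |
|---|---|---|---|
| 3% (control rate; matches 1320) | 1.51 | 0.91 | 4.0 |
| 4% (average; half of the site-months are intervention) | 1.74 | 0.82 | 3.6 |

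Taking the variance wholly at the 5% intervention rate would give 0.74, but half of the site-months are control. Trial success requires both co-primary tests, so every successful trial is on the cost-only branch.

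**3. What that branch leaves out.** At the planning values the differences are 5% − 3% = 2 points, or 20 extra re-visits per 1,000 children in that outcome's denominator, and 50% − 0.8 × 50% = 10 points, or 100 fewer admissions per 1,000. Resource use is not lost. Data collection and management includes physician visits, medication and hospital stays from one week before to one week after the trauma. Presentation within 48 h plus 72 h after ED discharge is 120 h, and the ED stay is added to that, against a window of 168 h. What is missing is the effect side and its joint distribution with cost.

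**4. The sections side by side.** Secondary outcomes lists cost-effectiveness, the Discussion promises it, and Healthcare economic evaluation provides for it only after non-inferiority fails, and then as an option. The article gives no unit costs, so no cost-effectiveness ratio can be illustrated here.

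**The case against.** The strongest reply is that the plan does not expect worse health. It attributes the extra re-visits to parents seeking reassurance, regards them as less of a burden than admission, and aims for equivalent medical safety. Re-visits are then mainly resource use, and that is costed. The switch is fixed in advance, the re-visit difference with its confidence interval is reported in any case as a co-primary result, and an article condenses what a fuller plan may elaborate.

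Much of this stands. It limits the point to the economic evaluation and to the effect side of it. It does not remove the point. The trial itself treats re-visits as its safety outcome, the rule is a stated choice and not an omitted detail, and the unspecified sensitivity analyses do not say that effects will be set against costs when non-inferiority is shown.

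A reader might go further in three ways that the document does not support:

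- **That a known difference is ignored and cost-effectiveness is never estimated.** The 2 points are a planning value. A trial that misses non-inferiority may run the analysis, and nothing forbids one otherwise.
- **That the cost-only result is over-precise.** Its interval can be correct for the cost difference; it answers a narrower question.
- **That re-visits significantly above zero would often be treated as equal.** With SE fixed at 5/(1.960 + 1.282) = 1.54 points, observed increases between 3.02 and 3.98 would qualify, about 23% of trials at a true +3. But variance rises with the rate. At the average of 3% and 6%, SE is 1.84, and the observed increase would have to be above 3.60 and below 3.40, which is impossible. That figure should not be used.

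**Conclusion.** The point holds as an inconsistency between the chosen economic analysis and the plan's own assumptions and stated outcomes. If the trial succeeds, the economic evaluation as written compares costs only, and the listed cost-effectiveness outcome is left unestimated. At the planned 2-point increase this branch is taken in about 82% to 91% of trials. An observed increase of up to about 3.6 to 4.0 points would still lead there.

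These figures rest on the stepped-wedge formula, an ICC of 0.1, full recruitment of 1320 evaluable children and the two variance choices shown. The argument itself does not depend on the exact percentage: non-inferiority within a 7-point margin is not evidence of equal effects. The co-primary tests, the sample size and the safety conclusion are unaffected.

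**What to change.** In Healthcare economic evaluation, make the joint analysis unconditional:

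- Report incremental cost together with incremental effect and their joint uncertainty, on a cost-effectiveness plane or as net benefit, whatever the non-inferiority result.
- Keep the cost-only figure as the case of zero effect difference.
- State that children with linked billing data are a subset (those insured with a participating fund), and show the full-trial effect estimate alongside the one from the subset.
- Report re-visits and admissions avoided in natural units. Say that their resource use is already in the cost term, so that any monetary value placed on them does not count the same events twice.
- Reconcile Secondary outcomes, Healthcare economic evaluation and the Discussion, so that cost-effectiveness is either estimated in every case or not promised.

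The cost is a change of wording and a little extra analysis on data already planned for linkage. No further patients are needed. The joint result will be less precise than a cost difference alone, particularly in the billing-linked subset, whose size the article does not give.

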##### Process evaluation

To identify existing barriers for the implementation of the nCP and to develop strategies for overcoming these barriers, a mixed-methods approach combining qualitative and quantitative methods will be applied. Focus groups including parents, adolescents, physicians and ED nursing staff will be conducted using a semi-structured interview guideline for approximately 60 min per group. The recorded conversations will be qualitatively analyzed with MAXQDA software (VERBI Software GmbH, Berlin, Germany) and used to design standardized questionnaire for surveys with parents and ED staff. For the analysis of parent and staff surveys, uni- or bivariate descriptive analyses will be conducted. Depending on the type of variable, frequency distributions with central tendency and variability measures (mean, median, variance, standard deviation) will be compared. Statistical significance will be determined using appropriate statistical tests. Subgroup analyses and correlation analyses will also be performed. Healthcare policy recommendations to incorporate the nCP into statutory health insurance portfolios will be derived from the mixed methods approach and discussed in a stakeholder workshop.

### Monitoring

Patient recruitment will be monitored by the study coordinators monthly. In addition, site-specific standardized operating procedures will ensure implementation of the study protocol at each study site, monitored by the study coordination. In turn, the study coordination regularly reports to the funder about achieved recruitment and any study incidences quarterly.

A dedicated data monitoring committee is not installed, because the documentation by the local physicians includes mainly anamnestic and physical assessment data that can only be monitored by observing the physical examination itself. Due to the study population and the low target number of inclusions per month, logistics to ensure the monitoring of an adequate number of cases per study site is not possible to achieve within the scope of the funding. In turn, the eCRF is designed to be intuitive for physicians and includes predominantly single- or multiple-choice answers with cross validation of data items and validation ranges for continuous variables. Further, intensive training for study personnel will be provided by the study lead with ongoing in-person support throughout the entire study period. No interim analyses are planned but plausibility checks of entered data will be performed regularly. No stopping rules have been determined, because the care pathway provides the option of switching to standard care (hospitalization) and performing additional diagnostic and therapeutic measures at any time. Moreover, the co-primary outcomes are specifically designed to evaluate the success of reducing hospitalizations and its safety.

### Confidentiality

The study sites ensure pseudonymization and keep pseudonymization at their site, protected against unauthorized access. The study sites transmit personal data and the pseudonym of study participants who are insured with one of the participating health insurance companies to the respective health insurance company for the purpose of health economic evaluation. Besides this, only pseudonymized data are transferred with no possibility for the study lead or any non-local investigator to identify participants.

